# Piloting and evaluating feasibility of a training program to improve patient safety for inter-professional inpatient care teams – study protocol of a cluster randomized controlled trial

**DOI:** 10.1186/s13063-019-3448-7

**Published:** 2019-06-28

**Keywords:** Patient safety, Inpatient care, Inter-professional teamwork, Patient involvement, Error management, E-learning, In-person training, Cluster randomized controlled trial, Evaluation

## Abstract

**Background:**

Improving patient safety is a major goal in healthcare systems worldwide. There are several international training programs to improve patient safety, but they are often focused on single topics and professions. Therefore, one inter-professional training program for inpatient care teams, which combines key areas of patient safety (Teamwork, Error management and Patient involvement), was developed by our research group. In the present study we aim to (1) pilot this training program by comparing two different training formats (e-learning only versus blended learning) with a waiting control group and (2) evaluate the feasibility of the intervention.

**Methods and analysis:**

(1) To pilot the intervention a cluster randomized controlled trial will be performed at three study sites. Therefore, an e-learning group and a blended learning group will be compared to a waiting control group at three points of assessment; (2) The feasibility of the intervention will be evaluated using qualitative methods. We will conduct problem-focused individual interviews as part of the post-intervention measurement in order to collect information on acceptance, implementation, promoting factors and barriers from the staffs’ perspective.

**Discussion:**

The study puts forth a training program which has the potential to improve patient safety in inpatient care. Members of inter-professional inpatient care teams can receive systematic training in three competencies which are central to patient safety management. Thus, we expect the greatest improvement in staff Safety-related behavior regarding Teamwork, Error management and Patient involvement as well as Subjectively perceived patient safety in the blended learning group. In addition, the development of an optimal implementation strategy can foster implementation of the intervention in healthcare practice. Consequently, the intervention could be used continuously and comprehensively for advanced training of hospital staff.

**Trial registration:**

The study has been registered in the German Register of Clinical Trials (DRKS-ID: DRKS00012818). Registered on August 8, 2017.

**Electronic supplementary material:**

The online version of this article (10.1186/s13063-019-3448-7) contains supplementary material, which is available to authorized users.

## Background

Improving patient safety is a major goal in healthcare systems worldwide [1]. Patient safety can be defined as the “avoidance, prevention and amelioration of adverse outcomes or injuries stemming from the process of healthcare” [2]. The World Health Organization has stated that 134 million adverse events occur each year in hospitals, contributing to 2.6 million deaths annually due to unsafe care [3]. Internationally, a wide range of interventions for improving patient safety exist, putting a particular emphasis on developing training programs [4]. Existing international training programs often focus on single professions as well as a specific patient safety topic, e.g., teamwork (Strategies and Tools to Enhance Performance and Patient Safety – TeamSTEPPS, USA) [5, 6], Speak up initiatives (USA) [7–9], patient involvement (Patientenempfehlungen (Recommendations for patients) – PATEM, Switzerland) [10]. To the best of our knowledge, there is no inter-professional training program for inpatient care teams which covers different key areas of patient safety. However, due to the complexity of patient safety, a reduction to the most important contents was necessary. Therefore, focus groups were established by our research group to find out the requirements of an inter-professional, multi-content, training program in Germany [11]. The main findings of the study were the training format and recommendations regarding the content: The training should be a combination of e-learning and interactive in-person training (blended learning), with the content focused on *Teamwork*, *Error management* and *Patient involvement* [11]. These recommendations are consistent with the Patient Safety Curriculum Guide [1] and the Learning Objective Catalog for Patient Safety [12], which define these as the three key areas, among others. If we look into the literature, a considerable amount of evidence can be found confirming these topics as the three key areas. Current research shows that training programs can provide new insights and improve attitudes toward teamwork [13–17]. Improving teamwork can lead to increased patient satisfaction [18], employee satisfaction [19] and employee well-being [20], more efficient patient treatment [21] as well as to decreased medical errors [22] and mortality [23]. By improving communication within the team of healthcare professionals and with patients, such programs can also contribute to improvements in healthcare delivery and make healthcare safer [17, 24–31]. Furthermore, discussions and reflections of adverse events, errors and their consequences for patients can build the foundation for open communication and thus a practiced safety culture [32]. With regard to patient involvement, patients have been found to possess the willingness, ability and desire to play an active role in error prevention in accordance with their capabilities [28, 33–36]. However, this willingness is closely linked to positive attitudes of the inpatient care team concerning open communication about errors and patient involvement as well as to their social and communicative competencies [37–39]. In total, all three topics are mutually dependent on each other and lead to better patient safety.

The KOMPAS project (KOMPAS = German acronym for “Development and evaluation of a complex training program to improve patient safety”) takes a first step to close this gap by designing a training program according to the stated criteria by using innovative adult education methods. Moreover, an optimal implementation strategy can foster the implementation of the intervention in healthcare practice by overcoming potential barriers. The present study aims to (1) pilot the training program by comparing two different training formats with a waiting control group (WCG) and (2) evaluate the feasibility of this intervention.

### Research questions

In the course of piloting the intervention, the following research question and hypothesis will be pursued:To what extent can the intervention be used to improve Safety-related behavior with regard to Teamwork, Error management and Patient involvement?H1: The improvement of Safety-related behavior with regard to Teamwork, Error management and Patient involvement in IG1 (intervention group 1: e-learning only) and IG2 (intervention group 2: combined e-learning and in-person training = blended learning) is significantly higher than in the WCG.In the e-learning course, the participants will work individually on the theoretical foundations for the three key areas. Due to the additional in-person training, the participants will try out and consolidate their knowledge. This leads us to the following hypothesis:H2: The greatest improvement in Safety-related behavior with regard to Teamwork, Error management and Patient involvement is in IG2 (intervention group 2: combined e-learning and in-person training = blended learning)To what extent can the intervention be used to improve Subjectively perceived patient safety?H3: The improvement of Subjectively perceived patient safety in IG1 (intervention group 1: e-learning only) and IG2 (intervention group 2: combined e-learning and in-person training = blended learning) is significantly higher than in the WCGH4: The greatest improvement of Subjectively perceived assessed patient safety is in IG2 (intervention group 2: combined e-learning and in-person training = blended learning)With regard to evaluating the feasibility of the intervention the following research question should be answered:Which facilitators and barriers for successful implementation of the intervention can be identified?

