## Methods and analysis

### Study design

According to the Medical Research Council Framework for Developing and Evaluating Complex Interventions [40], the study is classified as Phase 2 (Feasibility and Piloting).

To pilot the intervention, a cluster randomized controlled study will be performed. Cluster units will be wards at the participating hospitals. The cluster design was selected as it is considered the best option if an individual randomization is not possible. For methodical, ethical and organizational reasons, the same intervention must be offered to all staff on a ward, otherwise there is a risk of contamination [41]. Prior to data collection, inpatient care teams from the participating wards (clusters) at the three study sites will randomly be assigned the to: (1) an e-learning group (intervention group 1; IG1), (2) a blended learning group (combined e-learning and in-person training; intervention group 2; IG2), or (3), a WCG based on computer-generated randomization sequence with a 1:1:1 treatment allocation ratio, stratified by center. To ensure concealment, central randomization with variable block sizes will be conducted by an independent statistician not involved in recruitment or implementation of the intervention. Both representatives of the clusters and work councils sought consent before randomization. Data will be collected at three points of assessment: (1) prior to the intervention (pre-measurement), (2) 12 weeks post intervention (post-measurement), and 24 weeks post intervention (follow-up measurement). Figure 1 illustrates the study process.

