### Sample size

As the anticipated effect of the intervention on the primary and secondary outcomes is unclear, one of the aims of the feasibility study is to estimate this effect, in preparation for a confirmatory study [40]. Thus, the required sample size is determined on the basis of the identification of important rare (predicted or unpredicted) events [42]. In order to identify an event which occurs in 10% of cases with a confidence interval of 95%, 30 people have to be investigated in each relevant subgroup [42]. A conservative minimum of 10 employees per inpatient care team on the wards (cluster) will be taken as a starting point, so the three study sites each comprise nine wards (three per study arm). This means that viable data from a total of 90 participants (30 in IG1, IG2 and WCG, respectively) must be collected at each study site. As we anticipate a dropout rate of up to 25%, 12 wards will be recruited at each study site and randomly assigned to the three study arms. Thus, the study will in total include 36 wards with a minimum of 360 participants across three sites (10 participants * 4 wards * 3 study arms * 3 study sites).

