### Outcomes

The primary outcomes in the pilot study are *Safety-related behavior regarding Teamwork, Error management and Patient involvement* and S*ubjectively perceived patient safety.* The secondary outcomes are aspects of *Teamwork*, *Error management* and *Patient involvement*.

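### H1 and H3 promise a significance verdict from a pilot that is described, and sized, for feasibility and estimation

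*Protocol article*

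**What the plan says.** **Hypotheses (Research questions).** H1 concerns safety-related behavior in three areas and ends "combined e-learning and in-person training = blended learning) is significantly higher than in the WCG". The second primary outcome is treated in the same way: "H3: The improvement of Subjectively perceived patient safety in IG1" and IG2 is again predicted to be significantly higher than in WCG. H2 and H4 are worded differently. H2 reads "H2: The greatest improvement in Safety-related behavior with regard to Teamwork, Error management and Patient involvement is in IG2", which is an ordering without a significance claim, and H4 does the same for perceived patient safety.

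**Outcomes.** Two primary outcomes are named: "The primary outcomes in the pilot study are *Safety-related behavior regarding Teamwork, Error management and Patient involvement* and S*ubjectively perceived patient safety". The article does not say whether the three behavior areas form one score or three.

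**Design (Study design).** There are three arms, "with a 1:1:1 treatment allocation ratio, stratified by center", with measurements before the intervention and 12 and 24 weeks after it. In the same section, "the study is classified as Phase 2 (Feasibility and Piloting"). The text after Figure 1 adds that the effect and the intra-cluster correlation will be estimated so that a future confirmatory study can be sized.

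**Sample size.** The section opens "As the anticipated effect of the intervention on the primary and secondary outcomes is unclear". It then bases the number on seeing an event of 10% frequency, with 30 people per subgroup.

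**Data analysis.** Inferential analyses are planned, using a linear mixed model with a group-by-time interaction and a random intercept for ward.

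**The concern.** A hypothesis that an improvement is significantly higher is answered yes or no by a p-value. The other sections say that the trial is meant to deliver estimates, and its size has no link to any effect. A reader of the results could not tell whether a p-value for H1 or H3 is the trial's answer on effectiveness or a by-product.

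Both possible errors matter. Several scores, two intervention arms and two later time points give several chances of a significant result if the training does nothing. If the training has a modest effect, a non-significant H1 could be read as failure when the trial had little chance of showing it. Either reading could colour how the training is judged before a confirmatory study.

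**Working it through.** **1. The plan's own figure.** The smallest n that shows a 10% event at least once with 95% probability is ln(0.05)/ln(0.9) = 28.4, so 29. With 30, the probability is 1 − 0.9^30 = 0.958. Nine wards per site with 25% dropout give 9/0.75 = 12 wards, and 10 × 4 × 3 × 3 = 360. The stated size reproduces, and no treatment effect, SD, power or significance level enters it.

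**2. How many comparisons H1 and H3 cover.** Two contrasts with WCG (IG1, IG2) at two later times give 4 comparisons per score:
- 2 scores (behavior as one score, plus perceived safety): 2 × 4 = 8
- 4 scores (three behavior areas, plus perceived safety): 4 × 4 = 16

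The article does not fix the number of scores, so both cases are shown.

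**3. False results under no effect.** Assumptions, none of which is stated in the article: two-sided 5% tests without adjustment; normal estimates of change in each arm; correlation 0.5 between the two times; correlation 0 to 0.7 between scores. For each score and time, z = (arm − WCG)/√2, and a result favours training if z > 1.96. Both contrasts share the control arm. Simulated proportions of null trials:

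| Scores | Comparisons | At least one result favouring training over WCG | Both arms beat WCG on the same score and time |
|---|---|---|---|
| 2 | 8 | 13% to 16% | about 2% |
| 4 | 16 | 19% to 29% | about 3% to 4% |

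The lower ends belong to correlation 0.7 between scores, the upper ends to correlation 0. A single prespecified contrast would give 2.5% in the favourable direction.

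**4. The reading closest to the stated model.** With one group-by-time interaction test per score, treated as independent, the chance of any significant test is 1 − 0.95² = 9.8% (2 scores) or 1 − 0.95⁴ = 18.5% (4 scores).

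**5. Power.** The protocol's target is 30 evaluable participants per arm and site, so 30 × 3 = 90 per arm. Assumptions: effect 0.3 SD, 10 per ward, intra-cluster correlation (ICC) 0 to 0.10, comparison of two means. Design effect = 1 + (10 − 1) × ICC; n_eff = 90/design effect; power = Φ(0.3 × √(n_eff/2) − 1.96). The difference detectable with 80% power is (1.96 + 0.84) × √(2/n_eff).

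| ICC | Design effect | n_eff | Power at 0.3 SD | Detectable with 80% power |
|---|---|---|---|---|
| 0 | 1.00 | 90.0 | 52% | 0.42 SD |
| 0.05 | 1.45 | 62.1 | 39% | 0.50 SD |
| 0.10 | 1.90 | 47.4 | 31% | 0.58 SD |

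If both arms must beat WCG on a given score and time, power cannot exceed these values.

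**The case against.** The strongest defence is that the exploratory purpose is already clear. Study design, Sample size and Discussion all point to a later confirmatory study, and the research questions above the hypotheses ask to what extent the training helps, which is the language of estimation. The missing primary contrast, time point and multiplicity rule may stand in an analysis plan that is not shown. That last part stands: their absence from a condensed article is not held against the plan here. The rest does not remove the conflict, because an analysis plan that named a contrast would still leave H1 and H3 promising a significance verdict.

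A reader might go further in four ways that the documents do not support.

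- **That all four hypotheses are significance claims.** H2 and H4 contain no such wording.
- **That a false significant improvement is likely.** Counting 24 comparisons (four scores, three arm contrasts, two times) gives 47% to 62% for any significant result under the same assumptions. That count is constructed, and it includes results in which WCG beats training or IG1 beats IG2, which contradict the hypotheses. Results in the predicted direction come to 27% to 39% even then. Read literally, H1 and H3 require both arms to beat WCG, and on the same score and time this happens by chance in only about 2% to 4% of trials.
- **That the lack of sizing for an effect raises the false-positive rate.** It does not. It lowers power; several comparisons raise the false-positive rate.
- **That the confirmatory study hangs on a p-value.** No section says so. The stated use of the results is to size that study from the estimated effect and ICC.

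Nor is a non-significant result worthless: effects of about 0.42 to 0.58 SD would be detected with 80% power in a single unadjusted comparison.

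**Conclusion.** The point holds as a conflict within the article. H1 and H3 are stated as significance claims on two primary outcomes, two arms and two later times, and inferential analysis is planned, while the design, sample size and stated aims are those of an estimation pilot.

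The size of the problem is moderate and depends on how H1 and H3 are read. If any contrast with WCG counts, a false favourable result occurs in roughly 13% to 29% of null trials. If both arms must win together, false positives are rare, but for a given score and time a real 0.3 SD effect would be confirmed at most 31% to 52% of the time. The article does not say which reading applies, and a bare significance verdict is a poor summary under either.

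These figures rest on an assumed number of scores, assumed correlations, an unadjusted two-sided 5% level, an ICC of 0 to 0.10 and an effect of 0.3 SD. The conflict in wording rests on none of them.

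**What to change.** - Restate H1 and H3 as estimation aims: report the difference in improvement between each training arm and WCG, for each primary score at each later time, with a 95% confidence interval. Remove the word significantly from both.
- Present H2 and H4 as descriptive orderings of IG2 against IG1.
- State in Data analysis that all p-values are exploratory and support no conclusion on efficacy.

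The cost is wording, plus reporting the modification to the registry and ethics committee as the Dissemination section foresees. Sample size, design and model stay as they are. The downside is that the sponsor gives up an efficacy claim that the pilot was not sized to support.

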## Methods and analysis

### Study design

According to the Medical Research Council Framework for Developing and Evaluating Complex Interventions [40], the study is classified as Phase 2 (Feasibility and Piloting).

To pilot the intervention, a cluster randomized controlled study will be performed. Cluster units will be wards at the participating hospitals. The cluster design was selected as it is considered the best option if an individual randomization is not possible. For methodical, ethical and organizational reasons, the same intervention must be offered to all staff on a ward, otherwise there is a risk of contamination [41]. Prior to data collection, inpatient care teams from the participating wards (clusters) at the three study sites will randomly be assigned the to: (1) an e-learning group (intervention group 1; IG1), (2) a blended learning group (combined e-learning and in-person training; intervention group 2; IG2), or (3), a WCG based on computer-generated randomization sequence with a 1:1:1 treatment allocation ratio, stratified by center. To ensure concealment, central randomization with variable block sizes will be conducted by an independent statistician not involved in recruitment or implementation of the intervention. Both representatives of the clusters and work councils sought consent before randomization. Data will be collected at three points of assessment: (1) prior to the intervention (pre-measurement), (2) 12 weeks post intervention (post-measurement), and 24 weeks post intervention (follow-up measurement). Figure 1 illustrates the study process.

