### Study setting and recruitment

Hospitals geographically located in areas around the three study sites (Hamburg (North-West Germany), Bonn (Middle-West Germany) and Freiburg (South-West Germany)) can participate in the study. A list of study sites can be obtained from consortium leaders in Freiburg. Hospital recruitment will be organized non-randomly by each of the three study sites according to pre-defined criteria for participating wards: (1) inpatient care teams with a minimum of 10 members, (2) inpatient care teams with an inter-professional composition. Pediatric, emergency and intensive care wards will be excluded from participating in the study, as teamwork is highly regimented in pediatrics and emergency care, and patient involvement would not be comparable to other wards. Moreover, inpatient care teams with less than 10 members and mono-professional teams will be excluded. Participating hospitals will be asked to assign a local study coordinator, who supports the research team in local staff recruitment, organization of the intervention, and data collection at the wards. The following inclusion criteria for the participants are mandatory: (1) being a member of the participating inter-professional inpatient care team (e.g., physicians, nurses, physiotherapists, speech therapists, ergo therapists), (2) being at least 18 years old and (3) being fluent in German. Team members of mono-professional teams, team members under the age of 18 years and team members who are not able to speak German fluently will be excluded from participating in the study.

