### Measuring the outcomes

As part of piloting the intervention, all outcomes will be measured at the individual level. Primary and secondary outcomes will be assessed at three points in time (pre, post and follow-up) by an online survey for the purpose of a summative evaluation. It will take approximately 20 min to complete this survey. There is also a paper version of the survey available. For the primary outcomes, situational judgement tests [48–50] will be used. They were pretested within an expert workshop with different members of inter-professional teams (e.g., physicians, nurses, therapists). The situational judgement tests describe typical everyday situations specifying five possible realistic behaviors. The participants have to rank the behaviors in the way that they most likely would react (ranging from (1) this approach is closest to my reaction, to (5) this approach is the least of my reactions). The ideal sequence, based on results of the expert workshop, will be scored with 30 points (4*4 + 3*3 + 2*2 + 1*1 + 0*0). The worst sequence will be scored with 10 points (4*0 + 3*1 + 2*2 + 1*3 + 0*4). The secondary outcomes will be assessed by validated scales and single items from standardized questionnaires. (e.g., *Teamwork* = Abridged version of the Questionnaire on Working in a Team (FAT-K) [51], Revised Nursing Work Index (NWI-R) [52], Scale to assess knowledge integration problems in interdisciplinary project teams (WIP) [53]; *Error management* = Error Orientation Questionnaire (EOQ) [54], Safety Attitudes Questionnaire (SAQ) [55], German short version of the Attitudes towards Patient Safety Questionnaire (G-APSQ short) [56] Safety Organizing Scale (SOS) [57], Psychological Safety Questionnaire [58]; *Patient involvement:* ThinkSAFE Patient Safety Questionnaire [59], Provider-Patient-Relationship Questionnaire (PPRQ) [60]. Items will be answered on 5-point Likert scales (ranging from totally disagree (1) to totally agree (5). A list of all included questionnaires is provided in Fig. 3.

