### Data collection and management

To access the online survey regarding summative evaluation, all participants will receive an email with a unique link to the online survey at each time of assessment (pre, post and follow-up) (see Fig. 1) from the local study coordinator. Lists with contact details of participants will be stored by the local study coordinator at participating hospitals. None of the researchers at the study sites will have access to any contact information of the participants. If required, participants can download a paper version of the survey and return questionnaires by mail to the study sites. Moreover, wards that do not provide email access for participants will receive a paper version of the survey coded with the ward number for unambiguous allocation of returned surveys. With the latter option, questionnaires will be collected in a survey mailbox at the wards or can be mailed directly to the study sites. For ensuring the allocation of individual paper-pencil and online data for pre, post and follow-up surveys, participants will be asked to create an individual four-digit ID to be entered in the survey. In order to raise response rates at each time of assessment, participants will receive at least two reminders via email 2 and 4 weeks after the initial invitation to the survey. In case of distributed paper-pencil questionnaires, the local study coordinator will send at least two postal reminders or give verbal reminders in team meetings at the wards. In addition, a poster in the ward rooms will remind them to participate.

Online surveys (pre, post and follow-up) will be entered by participants and pseudonyms stored on the survey projects at QuestBack server park (located in Bremen, Germany), a BSI-certified data center ensuring stringent security requirements. Paper-based questionnaires collected at the three study sites will be entered to the online survey platform (Unipark) by researchers, following data entry rules agreed in the study consortium. For quality assurance, 10% of the paper-based survey entries will be reviewed independently by a second researcher at the study sites. After the completion of the data collection, raw data will be downloaded in analyzable formats such as IBM SPSS Statistics 25.

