### Data analysis

Quantitative data from the pilot study will be evaluated using descriptive and inferential statistical analyses. A linear mixed model will be applied with fixed effects for the intervention group, time (repeat measures), group * time interaction, and study site, and a random intercept for ward affiliation. This model includes the estimation of the intra-cluster correlation (ICC) for our outcomes to provide the basis for a larger confirmatory study in the future. If substantial baseline differences are detected between groups, the relevant variables will be included in the analytical model at the individual or ward level. Analyses will follow the intention-to-treat approach, including data from all participants. A sensitivity analysis will be performed to assess the robustness of the findings against different strategies for dealing with missing data and accounting for the amount (“dose”) of intervention received by the participants. Potential predictors and moderators will be explored in post-hoc analyses. The qualitative data from the problem-focused individual interviews focused on reviewing the feasibility of the intervention will be analyzed on the basis of a structured contents analysis in accordance with Mayring [65–67].

In order to increase validity of the results, we will use methodological triangulation [68]. Qualitative and quantitative data will be cross-checked to search for regularities.

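### Wards are allocated before the pre-measurement and nothing shown keeps the arm from staff until it is done, so survey participation and baseline answers may depend on arm

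*Protocol article*

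**What the plan says.** All references are to the Protocol article.

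- **Order of events (Study design).** Wards are allocated first: "Prior to data collection, inpatient care teams from the participating wards (clusters) at the three study sites will randomly be assigned". The assessments are then listed: "Data will be collected at three points of assessment: (1) prior to the intervention (pre-measurement", followed by measurements 12 and 24 weeks after the intervention. The first assessment is tied to the start of the intervention, not to randomisation.
- **Consent (Study design).** "Both representatives of the clusters and work councils sought consent before randomization". No other consent to the trial or survey is placed in time relative to randomisation.
- **Concealment (Study design).** "To ensure concealment, central randomization with variable block sizes will be conducted by an independent statistician not involved in recruitment or implementation of the intervention".
- **Local coordinator (Study setting and recruitment).** Each hospital names a coordinator "who supports the research team in local staff recruitment, organization of the intervention, and data collection at the wards". Under Data collection and management the same person sends the survey invitation: "all participants will receive an email with a unique link to the online survey at each time of assessment (pre, post and follow-up", with reminders at 2 and 4 weeks.
- **Outcome (Measuring the outcomes).** The primary outcomes are situational judgement tests: "The participants have to rank the behaviors in the way that they most likely would react".
- **Analysis (Data analysis).** A linear mixed model with a group-by-time interaction, intention-to-treat on all participants, and conditional adjustment: "If substantial baseline differences are detected between groups, the relevant variables will be included in the analytical model at the individual or ward level".

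**The concern.** In a cluster trial, concealing the sequence protects the choice of wards. It does not protect what happens inside a ward once its arm is known. If staff decide whether to answer the first survey after that point, the respondents may be a different mix in each arm, and they may answer with the coming training, or its absence, in mind.

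The arms differ enough in burden for this to be plausible. From the Intervention section, IG2 faces three 1-hour modules plus a 210-minute session (3 × 60 + 210 = 390 minutes), IG1 the modules only (180 minutes), and the waiting group nothing until after follow-up.

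H1 to H4 all concern improvement, so the pre-measurement is one side of every comparison. The estimated effect is also meant to inform the sample size of a confirmatory study, so a distortion here would be carried forward.

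**Working it through.** **1. Order of events.** The plan has no figure for this point, so the check is of sequence.

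- Allocation precedes data collection (Study design).
- The pre-measurement is the first of the three data collections (Study design).
- Hence the pre-measurement follows allocation. This needs no inference beyond the two statements.

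**2. Is the arm withheld until the pre-survey closes?**

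- Study design: concealment is central, with variable blocks and an independent statistician. It covers the sequence up to ward assignment.
- Study setting and recruitment: the coordinator helps with recruitment, training logistics and data collection. No blinding is stated.
- Data collection and management: the coordinator sends the link. Nothing is said about what staff know when they open it. With reminders at 2 and 4 weeks, some answers may come a month after the invitation.
- Discussion: selection is acknowledged only for hospitals and wards that choose to join, as a limit on external validity.

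None of these provides the safeguard.

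**3. How each mechanism reaches the group-by-time contrast.**

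- *Arm-aware answers.* If knowing the arm shifts the pre-score by s₁ in a training arm and s₀ in the waiting group, the change contrast moves by −(s₁ − s₀), less whatever part of the shift persists at post. The documents do not give the direction.
- *Arm-dependent participation.* Suppose a type of staff makes up a share of respondents that differs by g between arms, and its mean change differs from that of colleagues by d SD. The contrast is then biased by g × d. If the types differ only in stable level, d = 0 and the difference cancels, as far as the same mix answers at each occasion.

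**4. Illustration (all inputs assumed; none is in the documents).**

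- If 80% of waiting-group staff and 60% of IG2 staff respond, and the extra waiting-group respondents are a type absent from IG2, then g = (0.80 − 0.60)/0.80 = 0.25. With d = 0.4 SD, the bias is 0.25 × 0.4 = 0.10 SD.
- For g from 0.10 to 0.30 and d from 0.3 to 0.8 SD, the bias runs from 0.10 × 0.3 = 0.03 SD to 0.30 × 0.8 = 0.24 SD.

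**5. Scale.** The Sample size section plans 4 wards × 3 sites = 12 wards per arm, with at least 10 staff each. The standard error of a two-arm difference at one occasion is √{2[1 + (10 − 1)·ICC]/(10 × 12)}:

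| Assumed ICC | SE (SD units) |
|---|---|
| 0 | 0.129 |
| 0.05 | 0.155 |
| 0.10 | 0.178 |

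The upper part of the illustrated range exceeds one standard error and the lower part is negligible beside it.

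**6. Planned safeguards.** Intention-to-treat keeps respondents in their assigned arm but does not restore staff who never answered. The conditional adjustment works on measured variables, and so does not reach unmeasured motivation; adjusting for an arm-aware baseline score would not undo the shift in that score. Reviewing participation rates and sample comparability, as Study design promises, can reveal the problem but cannot prevent it.

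**The case against.** The strongest reply is that much of this rests on what is not shown. Figure 1, Figure 3 and the SPIRIT checklist could give the timing of enrolment and disclosure, and an article may leave that detail to a fuller protocol. This stands to the extent that no one can say the arm was in fact known at the pre-survey. It does not remove the order the text itself fixes.

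A reader might infer several stronger things that the documents do not support:

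- *That individual staff agree only after allocation.* The consent sentence is garbled, contains no word limiting it to representatives, and does not say from whom consent was sought. Staff recruitment is not dated. Later individual agreement is a reasonable inference, not a stated fact.
- *That the coordinator can pick participants.* Eligibility is ward-team membership, adult age and fluent German, and all staff on a ward are offered the same intervention. No discretion is described; what remains is differential response.
- *That the baseline is contaminated by training.* The pre-measurement precedes the intervention by definition. The issue is knowledge of the arm, not exposure.
- *That participation rates are confounded with arm.* Arm is randomised, so participation by arm is an effect of arm that the pilot can estimate.
- *That the bias is about 0.10 SD.* Every input is assumed, and no reason is documented why one type of untrained staff should change differently from another.

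It is also fair to say that this is a feasibility study and that re-sequencing may come late. The trial status records pre-measurement starting in July 2018 with completion expected in spring 2019, and the article appeared in June 2019.

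**Conclusion.** The point holds as an avoidable and unprotected risk. The text places every baseline answer after ward allocation, and no shown part of the article keeps staff or the coordinator unaware of the arm until then. Arm-dependent response or arm-aware answers would enter the contrast used for H1 to H4, and the planned analysis would not remove them.

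Bias is not demonstrated, and its size and direction cannot be derived from the documents. The SD figures show only that it could be anything from nothing to more than one standard error. The conclusion rests on two conditions: that the missing figures and checklist contain no withholding rule, and that staff learn their arm before answering. The feasibility aims are not undermined, since participation by arm remains estimable. This is a cheap improvement to make, not a fault that invalidates the trial.

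**What to change.** **Wards not yet started.** Fix the list of eligible staff and close the pre-survey. Only then generate the central allocation for that ward, or release it to the ward, its staff and the coordinator. State this order in the protocol, including when staff and coordinator learn the arm.

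**Wards already started.** Report eligible, invited and responding staff at the pre-survey by arm, present the response rates as an effect of arm, and state that these wards' baseline was collected after allocation.

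**Cost.** Central randomisation is already in place, the coordinator already holds the contact lists, and no sample-size figure changes. Training can be booked only once the pre-survey closes, which may add about 4 weeks per ward given the second reminder at 4 weeks. If few or no wards remain to start, the reporting step is what is left for this trial, and the changed order should be carried into the confirmatory study.
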